**Part 1: Background**

Fluticasone-salmeterol has long been approved for the treatment of chronic obstructive pulmonary disease (COPD). In the US, GlaxoSmithKline markets two different inhalers containing fluticasone-salmeterol: Advair Diskus (first approved in 2000) and Advair HFA (first approved in 2006). The former, a dry powder inhaler, is approved for the indications of both COPD and asthma, while the latter, a metered-dose inhaler, is only approved for the indication of asthma. However, a small randomized controlled trial showed that Advair HFA had similar efficacy to Advair Diskus when treating COPD.^1^ Yet, metered dose inhalers have also been associated with more errors than dry powder inhalers.

Given ongoing clinical uncertainty, we will analyze the comparative effectiveness and safety of fluticasone-salmeterol delivered via metered-dose inhaler (Advair HFA) vs dry powder inhaler (Advair Diskus) among patients with COPD treated in routine clinical practice. The primary effectiveness outcome will be first moderate or severe COPD exacerbation; the primary safety outcome will be first pneumonia hospitalization. Secondary outcomes will include the annual rate of total moderate or severe COPD exacerbations (analyzed separately and together), first moderate exacerbation, first severe exacerbation, and annual rate of total pneumonia hospitalizations.

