**Part 2: Protocol**

Protocol Version Date: 3/4/2024

Author(s): [name], [name], [name], [name], [name]

1. **Title:** The comparative effectiveness and safety of fluticasone-salmeterol via metered-dose vs. dry powder inhalers in COPD
2. **Core Research Team:** [name], [name], [name], [name], [name] (Implementation in the Aetion Evidence Platform: [name]; PI: [name])
3. **Aim(s)**

**Aim 1 (effectiveness):** To compare new users of fluticasone-salmeterol via metered-dose vs. dry powder inhalers on the outcome of first moderate or severe COPD exacerbation.

**Aim 2 (safety)**: To compare new users of fluticasone-salmeterol via metered-dose vs. dry powder inhalers on the outcome of first pneumonia hospitalization.

1. **Data source**: Optum Clinformatics claims database January 1, 2007-November 30, 2023. The study will begin in 2007 since that is the first full year after Advair HFA was approved (Advair Diskus was approved in 2000). Thus, both products were on the US market throughout the study period.
2. **Study Design Diagram:** see Appendix Figure 1
3. **Cohort Identification**

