**6.1 Cohort Summary**

All patients with COPD, defined by 3 outpatient claims or 1 inpatient claim in the prior 3 years (PPV 0.82 [0.72-0.89]),^2^ who initiated a prescription for fluticasone-salmeterol (Advair HFA) (exposure) vs. fluticasone-salmeterol (Advair Diskus) (referent) between January 1, 2007 and November 30, 2023. We will require a 180-day washout period for both the exposure and the referent. We will also require 180 days of continuous insurance coverage prior to cohort entry. We will include patients who received other therapy in the baseline period (whether single-agent inhalers [ICS, LAMA, LABA], LAMA-LABAs, or triple therapy). In other words, we will include patients who may be stepping up therapy (from monotherapy), stepping down therapy (triple therapy), or switching (from LAMA-LABA). Following other studies, we will exclude patients who are less than age 40 to increase the specificity of COPD diagnoses. This will help further ensure that patients entering the cohort are receiving triple therapy for COPD rather than another respiratory condition.

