***Study period:***

Baseline Period: The baseline period is defined as 180 days prior and up to and including the cohort entry date [-180, 0] unless otherwise noted in the design diagram.

Follow up Period: The follow-up period starts 1 day after the cohort entry date and continues until censoring. For further details on censoring, see section 8.2.

***Note:*** All diagnosis, procedure and generic names of drugs are given in the file named “Protocol Appendix.”

| Steps |  |
| --- | --- |
| **6.2.1** | **Patients with prescription for Advair HFA/Diskus**  *Advair HFA is the exposure and Advair Diskus is the reference* **(fills of both on cohort entry are not allowed)**  **Date of prescription is called the index date**  [assessed between January 1, 2007 and November 30,2023]  *Appendix Table 1 “Exposure definitions,” variables names: Advair HFA, Advair Diskus* |
| **6.2.2** | **Exclude patients who do not have continuous insurance enrollment during baseline period**  [assessed between 180 days prior up to and including index date (-180, 0)] |
| **6.2.3** | **Exclude patients with no prior diagnosis of COPD**  [assessed 3 years prior to and including the index date (-1095, 0)]  *Appendix Table 2 “Exclusion criteria,” variable name: Diagnosis of COPD* |
| **6.2.4** | **Exclude patients who are under the age of 40**  [assessed on the index date (0, 0)] |
| **6.2.5** | **Exclude patients who received another ICS-LABA script (besides Advair HFA or Advair Diskus)**  [assessed between 180 days prior up to and including index date (-180, 0)  *Appendix Table 2 “Exclusion criteria,” variable name: ICS-LABA besides Advair* |
| **6.2.6** | **Exclude patients who started a LAMA, LAMA-LABA, or ICS-LAMA-LABA on the cohort entry date**  [assessed on the cohort entry date (0,0)] |

1. **Covariates**

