The baseline covariate assessment period for all measures will start 180 days before cohort entry and will stretch up to and include the day of cohort entry with the following exceptions: (1) We will assess age, sex, race, region, year of cohort entry, and index prescription by a pulmonologist only on the day of cohort entry; (2) We will assess the presence of any prior asthma diagnosis using all available data and stretching up to (and including) the day of cohort entry. Diagnosis based covariates will be defined using any care setting and any diagnosis position unless otherwise specified. All codes for these variables are provided in Appendix Table 3, “Covariates.” The variable names are as listed below in Table 1. All variables listed below will be included in our propensity score model. We will use a missing indicator in our propensity score model in the case that data are missing for any covariates.

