| **3** | Prior diagnosis of asthma | GOLD guidelines recommend ICS-containing regimens for those with a prior diagnosis of asthma. This subgroup analysis seeks to examine the comparative effectiveness of Advair Diskus and HFA in this population where ICS-based regimens are thought to be particularly beneficial. | Addresses comparative effectiveness and safety in lower risk subgroup | None |
| **4** | Excluding patients with recent asthma diagnosis codes (in prior 3 years). | GOLD guidelines recommend ICS-containing regimens for those with a prior diagnosis of asthma. This subgroup analysis seeks to examine the comparative effectiveness of Advair Diskus and HFA in this population where ICS-based regimens are thought to be particularly beneficial. | Addresses comparative effectiveness and safety in lower risk subgroup | Low power |
| **6** | Spirometry before cohort entry | Maintenance inhalers are more likely to be effective for patients who have a proven diagnosis of COPD (as measured by spirometry). We want to examine whether, among patients with spirometry (i.e. patients most likely to benefit from inhaler therapy), there is any difference between Advair Diskus and HFA. | Addresses comparative effectiveness and safety in population enriched for COPD (closer to RCT population) | We do not know the actual measurements from the spirometry. |
| **7** | Index-prescription from a pulmonologist | Pulmonologists may be more likely to assign guideline-recommended therapy compared to other practitioners. We will examine whether Advair HFA has similar effectiveness to Advair Diskus among patients whose index prescription is from a pulmonologist. | Addresses generic quality in population enriched for patients who should be receiving guideline-concordant care. | Low power. |
| 8 | Cohort entry between 2007-2018 | This is the primary time during which Advair Diskus and Advair HFA were on the market without generic competition, limiting confounding from competing devices that patients might be alternatively prescribed. | Limits confounding from competing inhalers, providing a more direct comparison of Advair Diskus vs. HFA. | None. |

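### The no-recent-asthma subgroup relies on 3 years without an asthma code, but only 180 days of observed history are guaranteed

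*Protocol*

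**What the plan says.** The subgroup table, row 4, is "Excluding patients with recent asthma diagnosis codes (in prior 3 years"). Its only listed weakness is low power. The footnote to the table says that every subgroup is run both in patients who meet the definition and in those who do not, so row 3 (prior asthma diagnosis) also produces a no-asthma group. The Covariates section defines that status by a variable lookback: "We will assess the presence of any prior asthma diagnosis using all available data".

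The enrollment requirement is much shorter. Section 6.1 states: "We will also require 180 days of continuous insurance coverage prior to cohort entry". Step 6.2.2 applies the same rule over (-180, 0): "Exclude patients who do not have continuous insurance enrollment during baseline period". No section, row or footnote adds a longer requirement for any subgroup.

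The data source is given as "Optum Clinformatics claims database January 1, 2007-November 30, 2023", the same dates as the cohort entry window. On labelling, the Background says of Diskus that it, "a dry powder inhaler, is approved for the indications of both COPD and asthma", and of HFA that "the latter, a metered-dose inhaler, is only approved for the indication of asthma".

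The rationale in row 4 repeats that of row 3. It cites guideline advice for patients who have asthma and describes a population in which ICS is expected to help most.

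**The concern.** A rule that needs codes to be present and a rule that needs them to be absent behave differently when history is short. The COPD criterion, "defined by 3 outpatient claims or 1 inpatient claim in the prior 3 years", also looks back 3 years with only 180 days guaranteed, but missing history there can only keep a patient out of the cohort. In row 4, missing history lets a patient in: unobserved time counts as time without asthma.

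Row 4 and the no-asthma half of row 3 are where a reader would look to see how the devices compare in patients without asthma. If those groups hold an unknown share of patients with uncoded asthma, the result describes a mixed population. Weighting does not repair this. Uncoded asthma is unmeasured, and length of lookback is not among the Table 1 variables in the propensity score model.

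**Working it through.** The protocol states no figure for this point, so there is nothing to reproduce. The first two steps use only the protocol's windows and dates. The rest is an illustration under stated assumptions.

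**1. Guaranteed share of the window.** Row 4 needs 1095 days; section 6.1 and step 6.2.2 guarantee 180. 180 / 1095 = 16.4%, leaving up to 1095 − 180 = 915 days unobserved.

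**2. Calendar limit, if the stated data dates are literal.** From January 1, 2007, adding 180 days gives June 30, 2007, the first date on which the 180-day rule can be met. Adding 1095 days gives December 31, 2009, the first entry date with a full 3-year window. The entry window is 6178 days, so 1095 / 6178 = 17.7% of entry dates could not have a full lookback. This falls away if earlier claims are held.

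**3. Chance of missing a patient with asthma.** Assume asthma codes arise at rate L per year (Poisson). The chance of no code is exp(−L × 180/365) over 180 days and exp(−3L) over 3 years.

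| L (assumed) | 180 days | 3 years |
|---|---|---|
| 0.5 | 78% | 22% |
| 1 | 61% | 5% |
| 2 | 37% | 0.2% |
| 4 | 14% | about 0% |

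**4. Hidden asthma in the code-free group.** With true prevalence p and average miss probability m, the share is p·m / (p·m + 1 − p). Simplify history to either exactly 180 days or the full 3 years, and assume 40% of patients have the short history. At L = 1:

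- m = 0.4 × 0.611 + 0.6 × 0.050 = 0.274.
- Prevalence 30%: 0.3 × 0.274 / (0.3 × 0.274 + 0.7) = 10.5%.
- Prevalence 40%: 0.4 × 0.274 / (0.4 × 0.274 + 0.6) = 15.5%.
- With 3-year enrollment (m = 0.050), these become 2.1% and 3.2%.

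**5. Range.** With short-history shares of 20% to 60% and L from 0.5 to 4:

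- At 30% prevalence in both arms, hidden asthma as written runs from 1.2% (L = 4, 20% short) to 19.3% (L = 0.5, 60% short), with no difference between devices. With 3-year enrollment the range is about 0% to 8.7%.
- At 40% (HFA) against 30% (Diskus), the difference as written is 0.6 to 7.8 percentage points.
- At 60% against 30%, it is 2.8 to 26.3 points.

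**6. What full enrollment does not remove.** At L = 0.5 with prevalence 40% against 30%, the 3-year-enrolled group still holds 12.9% against 8.7%. The filter reduces the error; it does not remove it when asthma is rarely coded.

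**The case against.** The strongest objection is to the size. The 180 days is a minimum, and patients with longer histories are checked for longer. A patient with only 180 days of data must also have met the COPD definition inside them, by 3 outpatient claims or 1 inpatient claim. Three claims in 180 days is about 6 per year, and diagnosis covariates count any setting and position. If asthma were coded at that pace (assumed L = 6), the chance of a miss over 180 days is exp(−6 × 180/365) = 5%, and little hidden asthma would remain. This stands as a reason not to present any one percentage as the expected contamination. It does not remove the mismatch: the inpatient route needs only one claim, and nothing in the protocol shows that asthma is coded as often as COPD.

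A reader might infer that the contamination is greater in the HFA arm because HFA is labelled only for asthma. The protocol does not support that as a fact. It gives a label, not an asthma rate by device, and all patients must be at least 40 and meet the COPD definition. If HFA is chosen because of asthma, an asthma code near the index prescription may also be more likely, which would work the other way.

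A reader might also take row 4 to be the plan's only safeguard against asthma. It is not. The no-asthma half of row 3 is a second restriction, prior asthma is in the propensity score, and the age limit is meant to improve the specificity of the COPD diagnosis. Nor does row 4 promise an asthma-free group: it excludes recent codes, so asthma last coded more than 3 years ago stays in by design.

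Finally, the 2007 dates may only mark when the study begins. The protocol does not say that earlier claims are unavailable, and year of entry is in the propensity score. That point is a clarification only.

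**Conclusion.** The mismatch is real and can be read from the protocol alone: membership rests on absence of a code over 1095 days, of which 180 are guaranteed to be observed. Patients with asthma and short histories can enter the no-recent-asthma group, and the no-asthma half of row 3 shares the weakness.

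The size cannot be established. It depends on the distribution of history length, the asthma code rate and asthma prevalence, none of which is given; the illustrative range is wide and reaches nearly zero when asthma is coded often. A larger error for HFA is a plausible risk, conditional on a difference in prevalence or history length between devices. It is not a finding.

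The consequence is confined to interpreting these subgroups. It gives no ground for calling the primary cohort or primary analysis invalid. The change is worth making because it is specific and cheap. The copied rationale in row 4 is a separate, smaller error of wording.

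**What to change.** - Run row 4, and row 3 as a check, among patients with continuous enrollment over (-1095, 0). Apply the filter to both the asthma and the no-asthma halves; filtering one half only would make the two differ in enrollment as well as in asthma status.
- Report the observed lookback length by device, so that a reader can judge how much misclassification is possible and whether it could differ between arms.
- Keep the main cohort's 180-day rule unchanged.
- Rewrite the rationale in row 4 so that it describes patients without recent asthma codes and states the team's own reason for studying them.
- State whether claims before January 1, 2007 are used for lookback.

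The cost is an enrollment filter in two subgroup analyses, one descriptive table and a few edits of wording. The downside is smaller subgroups, made up of longer-enrolled patients who may differ from the full cohort; row 4 already lists low power. For row 3 the filter guarantees 3 years of history, while its definition still uses all available data, so it serves as a check and does not replace the planned analysis.

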| 9 | Cohort entry between 2019-2023 | This study period includes both the approval of the first generic fluticasone-salmeterol (Wixela Inhub) in 2019, as well as the COVID-19 pandemic (starting in 2020). These events could potentially confound our estimate of the ATE due to changes in treatment selection, as well as respiratory outcomes, care, and hospitalizations due to COVID-19. | Allows us to observe how the ATE changes relative to our overall estimate during a period that includes COVID-19 and a major generic approval, which could flag potential confounding in the overall cohort. | Changes in ATE are likely due to unobserved confounders rather than comparative intrinsic effectiveness/safety between the Advair devices. |
| 10 | Gender (Male/Female) | COPD severity, incidence, and care has been observed to vary across various demographic dimensions; large observational studies such as this allow us to observe patients who are often excluded from clinical trials.^22–26^ | Allows us to observe potential heterogenous treatment effects between different demographic groups that often have inadequate representation in RCTs. | None. |
| 11 | Race (White/Black/  Hispanic/Asian) |  |  |  |
| 12 | Age (less than 65 vs. 65 and older) |  |  |  |

*Each subgroup analysis will be performed with patients who meet the definition (for example, at least 1 baseline COPD exacerbation) and those who do not meet the definition (for example, no baseline COPD exacerbations).

1. **Sensitivity analyses**

|  | **Sensitivity** | **Why?** | **Strengths** | **Weaknesses** |
| --- | --- | --- | --- | --- |
| **1** | Alter the grace period for continuous use (30 days, 90 days). | This allows us to assess whether estimates differ when the exposure definition changes. | Using a shorter grace period (30 days) will provide more specificity with respect to the exposure while the longer grace period (90 days) will better reflect real-world practice. | 30-day grace period will exclude people who are truly exposed, while 90-day grace period will include people are not truly exposed |
| **2** | ITT over one year of follow-up | We will assess whether there are differences between Advair Diskus and Advair HFA in a truly real-world setting in which patients frequently discontinue therapy. | This analysis will allow us to avoid informative censoring. | Much of the included person-time will be unexposed person-time. |

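### The 2019-2023 subgroup is to be read against the overall estimate that contains it, which dilutes the visible period difference; the disjoint 2007-2018 estimate should be the comparator

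*Protocol*

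**What the plan says.** The study period in the protocol (Data source; Cohort Summary) runs from January 1, 2007 to November 30, 2023, and the overall estimate uses all entrants in that window. The Subgroup analyses table splits the window in two: row 8 is "Cohort entry between 2007-2018" and row 9 is "Cohort entry between 2019-2023".

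Row 9 is motivated by the first generic approval in 2019 and by COVID-19, both of which the protocol sees as possible sources of confounding. Its Strengths cell names the comparison: "Allows us to observe how the ATE changes relative to our overall estimate during a period that includes COVID-19 and a major generic approval". It then gives the purpose: "which could flag potential confounding in the overall cohort". The Weaknesses cell adds that a change in effect probably reflects unobserved confounders and not a true difference between the devices.

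The table footnote commits to both sides of each split: "Each subgroup analysis will be performed with patients who meet the definition (for example, at least 1 baseline COPD exacerbation) and those who do not". Under Statistical analysis, each HR comes from a weighted Cox model with treatment alone as predictor and a 95% confidence interval from cluster-robust standard errors. That section and the subgroup table give no threshold, test or variance for the row 9 comparison.

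**The concern.** Row 9 is the check the protocol names for whether the generic-entry and COVID-19 years disturb the pooled result. Its reference value is the pooled result itself, which those years have already moved. The more information the late period contributes, the more it can shift the pooled HR, and the smaller the gap between the late HR and that pooled HR becomes. A check on the pooled estimate should not fade as the late period gains influence on it. A reader who judges by eye how far the 2019-2023 HR lies from the overall HR would see less change than there is, and could be wrongly reassured about pooling all years.

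The two estimates also share patients and so are correlated. Comparing their two confidence intervals as if they were independent uses the wrong standard error for the difference.

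**Working it through.** The protocol gives no event counts, standard errors or subgroup power, so it has no figure of its own to reproduce. The dilution follows from the overlap; its size depends on assumed inputs.

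**Inputs**
- Study window: January 2007 to November 2023, 203 months (protocol, Data source).
- Late period: January 2019 to November 2023, 59 months (row 9). Its calendar-time share is 59/203 = 0.29.
- w, the late period's share of information: not given, so taken as 0.1, 0.29 and 0.5. The middle value is the calendar share, which need not equal the information share.
- True late-to-early ratio of HRs: assumed 1.25, so d = ln 1.25 = 0.2231.

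**Dilution.** Treat the overall log HR as an information-weighted average of the two period log HRs. This is an approximation for a weighted Cox model.

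- log HR(overall) ≈ log HR(early) + w·d
- log HR(late) − log HR(overall) ≈ (1 − w)·d
- log HR(late) − log HR(early) = d, whatever w is

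| w (assumed) | (1 − w)·d | Late vs overall, shown as | Late vs early, shown as | Shift of the overall HR from the early HR, exp(w·d) |
| --- | --- | --- | --- | --- |
| 0.1 | 0.2008 | 1.22 | 1.25 | 1.02 |
| 0.29 | 0.1584 | 1.17 | 1.25 | 1.07 |
| 0.5 | 0.1116 | 1.12 | 1.25 | 1.12 |

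The gap that row 9 displays falls as the shift in the pooled HR rises.

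**Variance.** If the late estimate has variance V_L and the overall estimate V_O, their correct (nested) difference has variance V_L − V_O. Treating them as independent gives V_L + V_O. With V_O = w·V_L, the standard error is too large by the factor √((1 + w)/(1 − w)):

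- w = 0.1: √(1.1/0.9) = 1.106; a nominal 5% comparison has a true level of about 3.0%.
- w = 0.29: √(1.29/0.71) = 1.348; true level about 0.8%.
- w = 0.5: √(1.5/0.5) = 1.732; true level about 0.07%.

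**Does the overlap itself cost power?** Take assumed standard errors of the log HR of 0.05 (early) and 0.08 (late).

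- w = (1/0.08²)/(1/0.08² + 1/0.05²) = 156.25/556.25 = 0.281
- V_O = 1/556.25 = 0.0018
- Late vs overall, nested: difference 0.719 × 0.2231 = 0.1605; SE = √(0.0064 − 0.0018) = 0.0678; z = 2.37
- Late vs early, direct: difference 0.2231; SE = √(0.0064 + 0.0025) = 0.0943; z = 2.37
- Late vs overall, wrongly treated as independent: SE = √(0.0064 + 0.0018) = 0.0906; z = 1.77

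Handled correctly, the nested and direct contrasts carry the same evidence, because effect and standard error shrink together. What remains is a diluted displayed effect and a variance that the reader has to know to use.

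**The case against.** The strongest reply is that the plan already holds what is needed. Row 8 supplies the 2007-2018 HR, the footnote commits to both sides of each split, and every HR comes with a 95% confidence interval. Each patient enters once, at the first qualifying claim, so the two period cohorts are disjoint and any reader can form the ratio. Row 9 also warns against reading a period difference as a device difference. All of this stands, and it makes the point minor. It does not change the fact that row 9 names the other comparator.

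Two stronger readings are tempting, and the documents do not support them.

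- **The check loses power.** A reader might infer this from the overlap. The loss (z of 1.77 against 2.37 above) appears only if nested estimates are tested as independent. The protocol states no such test; it speaks only of observing a change that could act as a flag.
- **The same fault runs through the demographic rows and creates a multiplicity problem.** Rows 10-12 say "Allows us to observe potential heterogenous treatment effects between different demographic groups", so those groups are compared with each other and not with a total that contains them. An interaction contrast for them may sit in a statistical analysis plan that is not shown. Nor does the protocol say that significance in one stratum and not in another will be taken as a difference. A count of chance findings that treats the strata as independent would not hold either, because they repeatedly divide the same patients.

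**Conclusion.** The point holds for row 9 only. The protocol names a comparator that contains the subgroup, so the displayed log-HR difference is reduced by the fraction w: 10% at w = 0.1, 29% at w = 0.29 and 50% at w = 0.5. The direction holds for any w between 0 and 1, given the weighted-average approximation. The size rests on w and on the illustrative ratio of 1.25, neither of which is in the document. Reading the two confidence intervals as independent would be conservative. This is a caution about use of the output, not a procedure the plan prescribes. Severity is minor, since row 9 supports the primary analysis and is not part of it.

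**What to change.** In the Strengths cell of row 9, replace the reference to the overall estimate with a comparison against the 2007-2018 estimate of row 8. Report the ratio of the two period HRs with a 95% confidence interval:

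exp{ log HR(late) − log HR(early) ± 1.96·√(SE_L² + SE_E²) }

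The standard errors come from the two period-specific models, with weights estimated within each period. Within-period weights matter because weights fitted to all years together can leave imbalance inside a period, which would blur a check aimed at confounding.

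The cost is one changed phrase and one extra reported ratio, with no new data or population. The interval may be wide: with the assumed standard errors of 0.05 and 0.08, a ratio of 1.25 would have a 95% interval of exp(0.2231 ± 1.96 × 0.0943), about 1.04 to 1.50. A wide interval should be read as an inconclusive check and not as evidence that the periods agree.

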**Secondary**

1. All-cause mortality
2. Annual rate of moderate or severe COPD exacerbations
3. Annual rate of moderate COPD exacerbations
4. Annual rate of severe COPD exacerbations
5. First moderate COPD exacerbation
6. First severe COPD exacerbation
7. Annual rate of hospitalizations for pneumonia
   1. Follow up and censoring

**Primary effectiveness and safety outcomes**: Follow up starts 1 day after the cohort entry date and continues until any of the following occurs:

(1) discontinuation of index therapy (with a 60-day grace period between fills and a 60-day exposure risk window)

(2) switch from exposure to referent or vice-versa

(3) initiation of a different inhaler regimen (ICS, LABA, ICS-LABA, LAMA-LABA, ICS-LABA-LABA)

(4) death

(5) the end of insurance coverage

(6) the end of data

(7) 365 days

1. **Statistical analysis**: For our primary balancing methodology, we will perform inverse probability of treatment weighting (IPTW) with stabilized weights using propensity scores estimated from an over-identified covariate balancing propensity score (CBPS) model. We specified a logistic regression model for the CBPS estimation procedure, including the variables in Table 1 as predictors of exposure.

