| **4** | Exclude the first 30 and 60 days after cohort entry. | Patients may receive ICS-LABAs when their symptoms are bad (but before a true moderate or severe COPD exacerbation). We will assess whether any differences between Advair Diskus and Advair HFA exist when we exclude these early exacerbations. | This allows us to focus on the long-term effectiveness of these maintenance therapies. | Follow-up time will be low because patients discontinue their inhalers so frequently. We may not have sufficient power to detect small treatment effects in this analysis. |
| **5** | Alter the definition of a moderate exacerbation: (a) require an office or ED visit before the prednisone fill; (b) require both prednisone (5-14 days) and a respiratory antibiotic; (c) count either a prednisone script (5-14 days) or a respiratory antibiotic script | This will allow us to assess the robustness of the results to variations of the outcome definition. | Each of these outcome definitions has been employed elsewhere in the literature. | (a) We will exclude many patients who have moderate COPD exacerbations but do not come into clinic. (b) We will exclude many patients who are having moderate exacerbations (antibiotics + steroids are only recommended for patients meeting specific criteria such as purulent sputum); (c) We will include patients who receive antibiotics for reasons having nothing to do with COPD exacerbations |
| **6** | Alter the definition of a severe exacerbation: allow for a COPD diagnosis in any position for the hospitalization | This will allow us to assess the robustness of the results to variations of the outcome definition. | The outcome definition in the primary effectiveness analysis may exclude patients who are having a COPD exacerbation but are admitted for a different primary reason (e.g. MI). | This is a less specific definition than the one we employed since many patients will have a code for COPD during a hospitalization even though they are not having an exacerbation. |

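### Sensitivity analysis 1 varies the grace period but not the separate 60-day exposure risk window, so its claimed gain in exposure specificity is largely untested

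*Protocol*

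**What the plan says.** Under Follow up and censoring (section 8.2), item (1), the Protocol censors at "discontinuation of index therapy (with a 60-day grace period between fills and a 60-day exposure risk window"). These are two settings. The grace period decides whether two fills belong to one episode of use. The exposure risk window is the time added after the last supply of that episode.

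Under Sensitivity analyses, row 1, the planned change is "Alter the grace period for continuous use (30 days, 90 days"). The stated reason is: "This allows us to assess whether estimates differ when the exposure definition changes". The stated strength is: "Using a shorter grace period (30 days) will provide more specificity with respect to the exposure". The stated weakness is: "30-day grace period will exclude people who are truly exposed, while 90-day grace period will include people are not truly exposed". The row does not mention the risk window, and neither does any other row.

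Two further entries in the same table bear on the point. Row 2 is "ITT over one year of follow-up". Row 4, on excluding early follow-up, warns: "Follow-up time will be low because patients discontinue their inhalers so frequently".

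**The concern.** In this setting, a more specific exposure definition means that less off-drug time is counted as exposed. For a patient who stops for good, that time is the tail created by the risk window. Shortening the grace period alone does not shorten this tail. Since the Protocol itself expects frequent discontinuation, many patients may be of this kind.

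What is at stake is how the result is read. Off-drug time in both groups tends to pull a comparison of two devices towards no difference. If row 1 gives hazard ratios close to the primary one, a reader will take this as evidence that the result does not depend on off-drug time. If the off-drug share was nearly the same in all three versions, the stability says little about that question.

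**Working it through.** The Protocol gives no follow-up, event or refill figure for this point, so there is no stated number to reproduce. The check applies the censoring rule itself.

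**Inputs from the Protocol.** Grace period G = 60 days and risk window R = 60 days (section 8.2, item 1); G = 30 and G = 90 (Sensitivity analyses, row 1); follow-up capped at 365 days (section 8.2, item 7).

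**Assumptions, not in the Protocol.** Each fill supplies 30 days. Gaps are counted from the end of supply. After each fill a patient never refills with probability q = 0.1, 0.3 or 0.5. Otherwise the gap to the next fill is exponential with mean m = 10, 25 or 45 days. Other censoring reasons are ignored.

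**Rule.** Follow-up ends at (end of the supply that precedes the first gap longer than G) + R, or at day 365 if that is earlier.

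**Step 1: one fill, never refilled.** Supply ends on day 30.

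| G | R fixed at 60 | Off supply | R = G | Off supply |
|---|---|---|---|---|
| 30 | 30 + 60 = day 90 | 60/90 = 67% | 30 + 30 = day 60 | 30/60 = 50% |
| 60 | day 90 | 67% | day 90 | 67% |
| 90 | day 90 | 67% | 30 + 90 = day 120 | 90/120 = 75% |

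With R fixed, the three versions are identical for this patient. The same holds for anyone who stops for good after fills with no gap over 30 days.

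**Step 2: one gap of 45 days.** Supply ends on day 30 and the refill is on day 75. With G = 30 and R = 60 the patient is classed as discontinued but followed to day 90, which is 90 - 75 = 15 days past the refill. With G = R = 30 follow-up ends on day 60, before the refill.

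**Step 3: nine refill patterns, 40,000 simulated patients each.** Each cell gives the change in mean follow-up against 60/60, then the off-supply share of person-time. Column heads are G/R.

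| q, m | 60/60 share | 30/60 | 90/60 | 30/30 | 90/90 |
|---|---|---|---|---|---|
| 0.1, 10 | 32% | -11%, 32% | +1%, 32% | -19%, 27% | +6%, 36% |
| 0.1, 25 | 46% | -34%, 44% | +15%, 46% | -46%, 38% | +21%, 49% |
| 0.1, 45 | 54% | -32%, 51% | +28%, 54% | -49%, 43% | +39%, 58% |
| 0.3, 10 | 45% | -7%, 45% | 0%, 45% | -23%, 34% | +16%, 52% |
| 0.3, 25 | 53% | -23%, 51% | +10%, 53% | -41%, 41% | +26%, 59% |
| 0.3, 45 | 58% | -23%, 56% | +19%, 58% | -43%, 45% | +38%, 64% |
| 0.5, 10 | 54% | -4%, 53% | 0%, 54% | -27%, 40% | +23%, 63% |
| 0.5, 25 | 58% | -13%, 57% | +6%, 58% | -37%, 44% | +29%, 65% |
| 0.5, 45 | 61% | -14%, 59% | +11%, 61% | -39%, 46% | +36%, 68% |

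Before rounding, the share falls by 0.3 to 2.4 points in the 30/60 runs and moves by less than 0.5 points in the 90/60 runs. With the window matched it falls by 4.8 to 14.4 points (30/30) and rises by 3.0 to 8.6 points (90/90). A second random seed changed the follow-up figures by less than one percentage point.

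**Why the share hardly moves.** With R fixed, a shorter grace period removes later supplied days as well as later gaps, and still leaves a 60-day tail. Follow-up gets shorter, but its mix of supplied and unsupplied days stays nearly the same.

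**The case against.** The strongest reply is that the Protocol nowhere says the window stays at 60 days. The 60-day value is given for the primary analysis and row 1 is silent. The row's remark that the 90-day version takes in people who are not exposed would also fit a window that moves with the grace period, and paired settings for a sensitivity run might be completed in an analysis plan that is not shown. This stands in part: the fixed window is the literal reading, not an express statement. But the Protocol names the two settings separately, changes one, and itself claims what the change will achieve, so the gap is in this document.

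A reader might also infer that row 1 barely changes the exposure definition at all. The documents do not support that. The grace period decides whether intermittent refillers are censored. Even with the window fixed, follow-up changed for 5% to 50% of simulated patients in the 30-day version and 0% to 31% in the 90-day version. The row is nearly inert only when gaps are short. What does not move is the off-supply share.

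Nor is row 1 the only analysis that bears on dilution, because setting the as-treated result beside the ITT result in row 2 is informative too. That comparison can only add unexposed time, however; it cannot show what happens when such time is reduced.

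Two smaller points also stand. Off recorded supply is not the same as unexposed: the Protocol itself says a 30-day rule loses people who are truly exposed. And in the 45-day example the days after the refill are supplied days, so that case shows awkward labelling, not dilution.

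**Conclusion.** The point holds in a limited form. As written, row 1 tests how intermittent refillers are handled, with mean follow-up changing by about -4% to -34% (30 days) and 0% to +28% (90 days). It does not test the off-supply tail after the last fill, and the off-supply share moves by about 0 to 3 points. The claimed specificity gain at 30 days, and the matching loss at 90 days, are therefore largely not delivered.

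This rests on the literal reading that the window stays at 60 days. The sizes rest on an assumed 30-day supply and assumed refill behaviour, and the true values could lie outside these ranges. The result for patients who stop for good with no earlier gap over 30 days follows from the rule alone and needs no refill model. The primary analysis is not affected; the weakness is in what this check can be said to show.

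**What to change.** In Sensitivity analyses, row 1, state the exposure risk window used with each grace period, and vary it with the grace period: 30/30 and 90/90 against the primary 60/60. Moving both together mixes two effects, so keep the grace-only runs (30/60 and 90/60) if these are to be separated. If only the grace-only runs are kept, reword the strength and weakness entries so that they describe the handling of refill gaps and not exposure specificity.

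The cost is one line of text and two extra settings. The 30/30 run will have less follow-up (19% to 49% less than the primary in the assumed patterns), hence fewer events and a wider confidence interval. It should be read for the direction and size of any shift in the hazard ratio, not for significance.
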